### Outcome measures

The primary outcome measures will be self-assessed depression using the Beck Depression Inventory (BDI-II) [35] and the Patient Health Questionnaire-9 (PHQ-9) [36]. PHQ-9 consists of nine items, each scored 0–3 and with a total score range from 0 to 27. PHQ-9 shows a sensitivity of 0.77 (0.71–0.84) and a specificity of 0.94 (0.90–0.97) [37]. BDI was constructed to assess the degree of depression in adolescents and adults, and consists of 21 questions [38]. The BDI has been extensively validated in various studies. A review of the BDI’s internal consistency estimates yielded a mean coefficient alpha of 0.86 for psychiatric patients and 0.81 for non-psychiatric subjects [39]. For psychiatric patients the test-retest reliability has been reported to range from 0.48 to 0.86, whereas the coefficients for non-psychiatric subjects ranged from 0.60 to 0.83 [39]. We will also administer the MINI [32]. This will be done via telephone to make participation possible for persons who live in all regions of Sweden. Moreover, an independent (blind) rating of clinical global impression-improvement scale (CGI) [40] will be performed. Hence, all patients will be interviewed again after the treatment period. All self-report measures will be administered via the Internet, which will facilitate 1-year and 2-year follow-ups. According to Thorndike *et al*. [41], self-report measures administrated via the Internet show good validity. We estimate a drop-out from completing the post-treatment measures of approximately 30%. This would lead to a reduced sample size of 84, which will maintain the estimated power. While the cross-over design will prohibit conclusions regarding specific long-term effects, the long-term effect of the new treatment format (that is smartphones) is not yet investigated, making the follow-up informative in the case both treatments are ineffective. Moreover, switching treatment will be optional and we will be able to investigate subgroups that only complete one of the treatments. The main outcome of interest in the study is if smartphone-enabled behavioral activation is superior to attention control (use of smartphone with no reference to depression or behavioral activation). We expect a moderate difference on the main outcome measures of depression. We also expect the number of responders (defined as a decrease according to Jacobson on the BDI-II [35] and PHQ-9 [36] and remission to lower levels of symptoms on the MINI-mood disorders section [32]) to be larger in the behavioral activation arm.

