### Sample size

We will include a total of 120 individuals. With 60 patients in each group, an effect size of Cohen’s *d* = 0.60 will be statistically significant (80% power, 5% level), which we will view as a clinically relevant difference between the two conditions.

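### Two primary outcomes serve one superiority question with no rule on whether one or both must succeed, so the error rate of the main claim is not fixed and the power statement belongs to neither scale

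*Protocol article*

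**What the plan says.** Under Outcome measures the protocol article names two primary scales of equal standing: "The primary outcome measures will be self-assessed depression using the Beck Depression Inventory (BDI-II) [35] and the Patient Health Questionnaire-9 (PHQ-9) [36". The same section poses a single confirmatory question: "The main outcome of interest in the study is if smartphone-enabled behavioral activation is superior to attention control".

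The Sample size section has one power statement. With 60 per group, d = "0.60 will be statistically significant (80% power, 5% level), which we will view as a clinically relevant difference between the two conditions". It names neither scale and does not divide the 5%. Outcome measures adds: "We estimate a drop-out from completing the post-treatment measures of approximately 30" per cent, leaving 84 participants, a number said to keep the power intact.

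Statistical analysis plans ANCOVA with the pre-treatment score as covariate, at post-treatment and at 1 year. It gives no significance level and no way of turning two results into one conclusion. Outcome measures also says that a moderate difference is expected on the main depression measures. That is an expectation, not a criterion for success.

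**The concern.** One claim of superiority can be reached by three routes: the BDI-II alone, the PHQ-9 alone, or both together. The routes have different false-positive rates and different power, and the article does not choose among them. If the scales disagree at week 8, no conclusion has been defined in advance, and the rule could be picked after the results are known. The stated 5% and 80% are properties of one test, so neither can be attached to the main claim until the rule is written down.

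**Working it through.** **Inputs from the article.** Two primaries; d = 0.60; 5% level; 80% power; 60 per arm; 30% dropout, so 120 × 0.70 = 84, or 42 per arm.

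**Assumptions.** Two-sided tests (sidedness is not stated). Correlation ρ between the two test statistics from 0 to 0.9 (not given). The same d = 0.60 on both scales for the power figures. Normal approximation.

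**1. The plan's own figure, one outcome.** Noncentrality λ = d·√(n/2); power ≈ Φ(λ − 1.96).
- 60 per arm: λ = 0.60 × √30 = 3.286, power 90.8% (t-test 90.3%).
- 42 per arm: λ = 0.60 × √21 = 2.750, power 78.5% (t-test 77.6%).

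The stated 80% is thus close to a single test in 84 completers, and conservative for 120.

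**2. False-positive rate if either scale suffices at 5%.** 1 − P(|Z₁| < 1.96 and |Z₂| < 1.96), with Z bivariate normal, means 0, correlation ρ. At ρ = 0 this is 1 − 0.95² = 9.75%. The table gives the rest. It counts errors in both directions; in the favourable direction alone the rate is 4.9% (ρ = 0) to 3.5% (ρ = 0.9), against 2.5% for one test.

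**3. If both are required.** The error rate is at most 5%, because each test alone is held at 5%. Power is P(Z₁ > 1.96 and Z₂ > 1.96) with both means equal to λ.

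| ρ (assumed) | Error, either suffices | Power, both required, 60 per arm | Power, both required, 42 per arm |
|---|---|---|---|
| 0 | 9.75% | 82.4% | 61.6% |
| 0.5 | 9.1% | 84.4% | 66.7% |
| 0.7 | 8.35% | 85.8% | 69.4% |
| 0.8 | 7.8% | 86.6% | 71.1% |
| 0.9 | 7.0% | 87.8% | 73.3% |

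**4. If either suffices without adjustment**, power goes up, not down: 95% to 84% at 42 per arm (ρ from 0 to 0.9).

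**5. Effect of the planned ANCOVA.** Adjusting for baseline multiplies the residual variance by 1 − r², where r is the pre-post correlation. The article gives no r. As an illustration, take r = 0.48 for both scales. This is the lowest BDI test-retest coefficient the article quotes for psychiatric patients; it is not a pre-post correlation in this trial. Then d becomes 0.60/√(1 − 0.48²) = 0.60/0.877 = 0.684, and λ at 42 per arm is 0.684 × √21 = 3.13. Both-required power is then 77% (ρ = 0) to 84% (ρ = 0.9), and a single test has 88%. The error rates in step 2 do not depend on r.

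**6. Holm, if both stay primary.** The smaller p-value is tested at 2.5% (critical value 2.241) and the other at 5%. Power for a given scale at 42 per arm, unadjusted for baseline, is at least Φ(2.750 − 2.241) = 69.4%, the Bonferroni figure. If both scales have d = 0.60, add P(1.96 < Z₁ < 2.241 and Z₂ > 2.241), which brings it to 75.7% (ρ = 0) down to 73.4% (ρ = 0.9), against 78.5% for a sole primary.

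**The case against.** The strongest reply has three parts.

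First, a reader might infer that each scale is tested at 5%, that a win on either is enough, and hence that the trial's error rate is not 5%. The article says none of this. The 5% appears once, in the sample-size statement, and no sentence says that one scale suffices. The plural in the expected difference, and a responder definition that joins the two scales, if anything lean the other way, though neither is a decision rule. This part stands: the error rate is undetermined, not shown to be inflated.

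Second, a reader might infer that requiring both scales breaks the stated 80% power. At the 60 per arm for which that figure is given, it does not: power is 82% to 88%. A shortfall arises only at 84 completers, and the 62% to 73% there leaves out the baseline covariate the plan will use. With an assumed pre-post correlation of 0.48, the shortfall is small or absent. This part also stands.

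Third, this is a condensed article and no analysis plan is shown, so a multiplicity procedure may sit elsewhere. That is fair for the details of adjustment. It does not cover the choice of primary outcome, or which hypothesis the sample size serves. Those belong in the protocol, and the article does fix them: two primaries, set against a power statement for one test. The objection is to that stated combination.

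**Conclusion.** The point holds in a limited form. The article names two primary outcomes for one question and does not say whether one or both must succeed. The false-positive rate of the main claim therefore lies anywhere from at most 5% (both required) to between 7.0% and 9.75% (either suffices at two-sided 5%, ρ from 0.9 to 0). Power likewise depends on the unstated rule. These figures rest on assumed between-scale correlations, two-sided testing and an equal effect on both scales.

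The documents do not show that the trial will exceed 5%, nor that it is underpowered at its planned enrolment. What they show is that the stated 5% and 80% cannot be assigned to the claim the trial intends to make. That matters for the main conclusion and is cheap to settle before post-treatment data are analysed.

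**What to change.** Before post-treatment data are analysed, add one sentence naming one scale at post-treatment (week 8) as the sole primary outcome, tested at two-sided 5%, with the other tested at 5% only if the first is significant. The BDI-II is one candidate, but its being listed first does not rank it; the choice is the sponsor's. If both are to stay primary, use Holm across the two. Then restate the power statement in the Sample size section for the outcome and rule chosen, at both 60 and 42 per arm.

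Either route holds the error rate at 5% and needs no more patients. Under the fixed sequence, a win on the second scale alone is supportive only. Under Holm, per-scale power is somewhat lower than for a sole primary: 73% to 76% against 78.5% at 84 completers, unadjusted, if both scales have d = 0.60, and no lower than 69.4% if only one does.

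### The stated 80% power for d = 0.60 is attached to 120 participants but roughly describes the 84 expected after drop-out; 120 give about 90%, so the two power statements need reconciling

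*Protocol article*

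**What the plan says.** The Sample size section sets 120 participants in two groups of 60. Of a standardised difference of d = 0.60 it says that it "will be statistically significant (80% power, 5% level), which we will view as a clinically relevant difference between the two conditions". The sentence opens "With 60 patients in each group", so the 80% is attached to the full enrolled number. It does not say whether the 5% level is one-sided or two-sided, or which test was used.

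The Outcome measures section expects roughly 30% of participants not to complete the post-treatment measures, and concludes: "This would lead to a reduced sample size of 84, which will maintain the estimated power".

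The Statistical analysis section plans an ANCOVA on the pre-treatment score for the between-group comparison. Neither power statement refers to that adjustment, and no baseline-post correlation is given.

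**The concern.** Two sample sizes that differ by 30% are given the same power for the same effect. For a fixed test, significance level and effect size, power rises with the number analysed, so at most one of the two attributions can be right.

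These two sentences are the article's whole justification of its sample size and its only assurance that the predicted attrition is tolerable. As written, a reader cannot tell whether 80% is the power before or after drop-out. On the first reading, the reader understates what complete follow-up would deliver. The reader also believes that losing 36 people costs nothing, when it costs about 13 points of power on the unadjusted test.

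**Working it through.** **Inputs from the protocol article.** d = 0.60, 5% level, 80% power and 60 per group (Sample size); about 30% drop-out and 84 remaining (Outcome measures); ANCOVA with the pre-treatment score as covariate (Statistical analysis).

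**Assumptions.** Two-sided test, equal arms, and drop-out balanced between arms. One-sided and split-level variants are shown below.

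**Step 1: the drop-out arithmetic.** 120 × (1 − 0.30) = 84, or 42 per group. This reproduces.

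**Step 2: power by the normal approximation.** Power = Φ(d·√(n/2) − 1.960).
- n = 60: 0.60 × √30 = 3.286; 3.286 − 1.960 = 1.326; Φ = 90.8%.
- n = 42: 0.60 × √21 = 2.750; 2.750 − 1.960 = 0.790; Φ = 78.5%.

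**Step 3: the same with the noncentral t distribution, and other readings of the 5% level.** The noncentrality is d·√(n/2), with 2n − 2 degrees of freedom.

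| Test, d = 0.60 | 60 per group | 42 per group |
|---|---|---|
| Two-sided 5% | 90.3% | 77.6% |
| One-sided 5% | 94.8% | 86.0% |
| Two-sided 2.5% (level split over the two primary outcomes) | 84.4% | 67.9% |

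No row gives 80% at 60 per group, and no row gives the same power in both columns. On the two-sided 5% test the fall is 90.3 − 77.6, about 13 points.

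**Step 4: the effect that has 80% power (t-test, two-sided 5%).** At 60 per group it is d = 0.52; at 42 per group it is d = 0.62.

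**Step 5: the number needed for 80% at d = 0.60.** By the normal formula, n = 2 × (1.960 + 0.842)² / 0.60² = 43.6, so 44 per group (88 analysed). By the t-test it is 45 per group (90 analysed, power 80.4%). The 84 expected are therefore 4 to 6 completers short on an unadjusted test.

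**Step 6: the planned ANCOVA.** If d is on the unadjusted standard deviation and r is the baseline-post correlation, the effective size is d/√(1 − r²). The values of r are assumptions.

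| Assumed r | 60 per group | 42 per group |
|---|---|---|
| 0.3 | 93% | 81% |
| 0.4 | 94% | 84% |
| 0.5 | 96% | 88% |

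At 42 per group, 80% is reached when 0.60/√(1 − r²) equals the 80%-power effect from Step 4 (0.6186 before rounding). That gives r = √(1 − (0.60/0.6186)²), about 0.24. Adjustment raises both columns, but power still falls from 120 to 84.

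**The case against.** The strongest reply is that the planners aimed for about 80% after drop-out and wrote that figure beside the enrolled number. Much supports this. The normal approximation at 84 gives 78.5%, close to 80%. The drop-out rate is itself approximate: at 25%, 120 × 0.75 = 90 would be analysed, and t-test power is 80.4%. The planned ANCOVA reaches 80% at r of about 0.24. The Outcome measures section cites test-retest reliability of 0.48 to 0.86 for the Beck inventory in psychiatric patients. Reliability is not a pre-post correlation under treatment, which may be lower, so this is indicative only; but r = 0.48 would give 87% at 42 per group. If 80% is read as a floor rather than as the power at each size, 120 clears it easily and 84 comes close or clears it.

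All of this stands against two stronger readings that a reader might infer. One is that 80% fits neither sample size; the other is that power at 84 has been shown to miss the 80% target. The documents support neither: 80% is roughly right for 84, and the shortfall appears only on an unadjusted test that is not the planned analysis.

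A reader might also take "We expect a moderate difference on the main outcome measures of depression" to mean d = 0.5, below the planned 0.60. The document puts no number on that word, and 0.60 can itself be called moderate, so no inconsistency follows.

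The reply does not rescue the text as written. The Sample size section does not present 80% as a floor or as a post-drop-out figure; it attaches it to 60 per group, where power is about 90%. The protocol also states no correlation on which a claim about the adjusted analysis at 84 could rest.

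**Conclusion.** The point holds as a misattached figure. For d = 0.60 on an unadjusted two-sided 5% test, 120 participants give about 90% power and 84 give about 78%. The stated 80% belongs approximately to the 84 completers, with a gap of 1.5 points (normal approximation) or 2.4 points (t-test). The Sample size and Outcome measures sections cannot both be right as statements of the power at their respective sizes, whichever test is used.

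The finding that 120 do not give 80% does not depend on sidedness or on splitting the level. The size of the shortfall at 84 does: it assumes two-sided testing at 5%, balanced drop-out and no baseline adjustment, and it disappears if r is about 0.25 or more.

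Severity is minor to moderate. No endpoint, analysis or enrolment number changes; what changes is how the trial's sensitivity is understood.

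**What to change.** Attach each power figure to its own sample size, and state the test, the sidedness and any assumed correlation. In the Sample size section, and in place of the sentence on maintained power in Outcome measures, text such as:

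> 60 per group gives about 90% power for d = 0.60 (two-sided 5%, unadjusted; 80% power at d = 0.52). After 30% drop-out, 42 per group gives about 78% unadjusted (80% power at d = 0.62), and at least 80% with the planned baseline-adjusted ANCOVA if the baseline-post correlation is about 0.25 or more (assumed).

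The cost is wording only. The figure at 120 becomes more favourable and the unadjusted figure at 84 slightly less so. No further enrolment is needed, which matters because the article reports that recruitment has ended.

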
### Moderators and mediators

As secondary outcome we will include the Beck Anxiety Inventory (BAI) [42], the Quality of Life Inventory (QOLI) [43] and Acceptance and Action Questionnaire (AAQ-II) [44]. The BAI is a 21-item self-report inventory for measuring the severity of anxiety in psychiatric populations [42]. De Beurs *et al.*[45] showed that the BAI has high internal consistency in panic patients (Cronbach’s a = 0.92) and good test-retest reliability (0.83). The QOLI consists of 16 areas rated by the subject concerning importance and satisfaction. The instrument’s internal consistency is high, between a = 0.77 and 0.89, and the 1 month test-retest reliability lies between r = 0.80 and 0.91 [43]. The AAQ-II is a 10-item, 7-point Likert scale that assesses psychological flexibility - a term for the ability to accept unwanted internal experiences and engage in valued actions. The AAQ II has shown good reliability (test-retest reliability = 0.81–0.87) and validity [44].

Other measures will be included as potential predictors of outcome such as education, number of previous episodes, and so on. Finally, we will include the Trimbos and Institute of Medical Technology Assessment Cost Questionnaire for Psychiatry (TIC-P [46]), which is a questionnaire designed to measure health related costs. Cost-effectiveness studies also often involved a measure called the EQ-5D [47]. The study will follow the guidelines given in the CONSORT statement [48,49], with the exception of double-blinding, which is not possible in psychotherapy studies. Other features such as intention-to-treat (mixed models approach [50]) and statistical power calculations will be adhered to. The theoretical rationale for smartphone supported behavioral activation is the observation that activity is related to depressive symptoms [8] and that behavioral change may be facilitated by the increased adherence provided by the smartphone.

### Statistical analysis

An intention-to-treat design will be used when analyzing post-treatment data and data collected at 1-year follow-up. Between-group changes at post-treatment and at 1-year follow-up will be calculated using analyses of covariance (ANCOVAs), with pre-treatment scores as the covariate. Effect sizes between and within the two groups will be calculated with Cohen’s d computed with the pooled standard deviation.

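### Two different intention-to-treat analyses are named, and the ANCOVA, followed as written, uses only participants with post-treatment scores

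*Protocol article*

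**What the plan says.** The protocol article addresses the analysis of randomised participants in four places.

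- **Statistical analysis:** "An intention-to-treat design will be used when analyzing post-treatment data and data collected at 1-year follow-up". The next sentence gives the method: ANCOVAs at post-treatment and at 1 year, with the pre-treatment score as covariate. Mixed models are not mentioned.
- **Moderators and mediators:** "Other features such as intention-to-treat (mixed models approach [50]) and statistical power calculations will be adhered to". ANCOVA is not mentioned.
- **Outcome measures:** "We estimate a drop-out from completing the post-treatment measures of approximately 30" per cent, followed by "This would lead to a reduced sample size of 84, which will maintain the estimated power". The same section plans a telephone MINI and a blind CGI rating, and adds: "Hence, all patients will be interviewed again after the treatment period".
- **Safety monitoring and reporting:** data from participants who decline to continue are to be deleted.

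No section says how a missing post-treatment score is handled.

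**The concern.** Two methods are given for the same intention-to-treat comparison, with no ranking. They treat a participant who has a baseline score but no post-treatment score differently. A mixed model keeps that person in the likelihood. An ANCOVA needs an observed outcome and leaves the person out unless a value is imputed.

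As written, the ANCOVA would therefore leave out about 36 of 120 randomised participants while carrying the intention-to-treat label. Observed-case here means people who completed the measures, not necessarily the treatment.

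The estimate of the primary comparison is at stake if missingness is related to outcome differently in the two arms. That is plausible because the arms differ in what they ask and offer. The active arm has an 8-week program with reported activities and some therapist contact, whereas the control arm has brief education and a recommended app. The article itself links guidance to preventing drop-out.

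**Working it through.** **1. The plan's own figures**

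Inputs: 120 randomised, 60 per arm, d = 0.60, 80% power, 5% level (Sample size); 30% without post-treatment measures, leaving 84 (Outcome measures). Sidedness is not stated, so two-sided is assumed.

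- Observed: 120 × (1 − 0.30) = 84, or 42 per arm. Missing: 120 − 84 = 36.
- Power, normal approximation: Φ(d × √(n/2) − 1.96), with n per arm.
- n = 42: 0.60 × √21 = 2.75; 2.75 − 1.96 = 0.79; Φ = 0.785 (t-test 0.776).
- n = 60: 0.60 × √30 = 3.29; 3.29 − 1.96 = 1.33; Φ = 0.908 (t-test 0.903).

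The stated 80% fits, or nearly fits, 84 observed cases. It does not fit 120 with outcomes. The power statement thus describes an analysis of those with post-treatment scores.

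**2. Size of the possible bias**

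Assumptions, none of them from the documents: true d = 0.60, pre-post correlation 0.5, and exactly 30% missing in each arm. The log-odds of missingness rise by a given slope per SD of worse post-treatment outcome. Simulation with 1,000,000 per arm, ANCOVA on observed cases:

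| Slope, active | Slope, control | Estimated d | Bias |
|---|---|---|---|
| 1 | 0 | 0.79 | about +32% |
| 0.5 | 0 | 0.71 | +18% |
| 1 | 0.5 | 0.68 | +13% to +14% |
| 0.25 | 0 | 0.66 | about +10% |
| 1 | 1 | 0.60 | none |
| 0 | 0 | 0.60 | none |

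If missingness depends only on the baseline score, even in the active arm alone, the estimate is also 0.60. If the steeper slope lies in the control arm, the bias runs the other way.

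**3. Would the mixed model help by itself?**

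A mixed model was fitted by maximum likelihood to everyone randomised in the 1-versus-0 scenario, with pre and post scores as outcomes and a common baseline mean. It gave 0.795, and the observed-case ANCOVA on the same data also gave 0.795. A person with only a baseline score carries almost no information on the week-8 contrast, so choosing between the two names changes little on its own.

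**4. Would the telephone ratings help?**

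Same 1-versus-0 scenario. Missing scores are imputed by arm from baseline and one interview rating, which is assumed to be obtained for everyone:

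- correlation of rating with outcome 0.6: estimate falls from 0.79 to about 0.74;
- correlation 0.8: estimate falls from 0.79 to about 0.69.

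The excess over 0.60 drops from 0.19 to 0.14 or 0.09. The correction is useful but partial.

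**The case against.** The strongest reply has four parts.

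- **Completer analysis is an inference.** A reader might state flatly that the trial plans a completer analysis. The article never says that missing cases are excluded. The figure of 84 is a power allowance, not a definition of the analysis set, and an analysis plan not shown could specify imputation. This stands, so the point is limited to what follows if the text is applied as written. An unseen imputation rule would not remove the conflict between the two named methods.
- **The largest bias is a chosen extreme.** It needs outcome-dependent missingness in one arm and random missingness in the other. No section gives a slope, an arm difference in drop-out or a pre-post correlation. This stands, and the range from zero is the fair statement.
- **Dilution of the effect.** A reader might argue that a d of 0.60 among those measured means 0.42 in all randomised (0.70 × 0.60 + 0.30 × 0), or 0.51 if the unmeasured gain half. The documents do not support this. The 30% are people expected not to complete the measures, and nothing says they gain nothing or half from treatment.
- **Two rival primary results.** A reader might infer wide freedom to pick the better answer. With only pre and post scores, the two estimates of the week-8 contrast virtually coincide, so little freedom arises from that choice alone.

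What remains is the contradiction itself, and silence on missing scores where about 30% are expected.

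**Conclusion.** The concern holds in a limited form. The article gives two unreconciled methods for intention-to-treat. Followed as written, the ANCOVA analyses about 84 of 120 under that label. Under the assumptions above, with the steeper dependence in the active arm, the bias for a true d of 0.60 lies between 0 and about +32%. It is nil when missingness depends only on baseline or equally on outcome in both arms. The documents do not show which case applies, so they do not support saying that the trial's result will be biased. The deletion of data from those who decline to continue pulls against intention-to-treat in its own right. This should be fixed; it does not invalidate the design.

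**What to change.** - Reconcile the Statistical analysis and Moderators and mediators sections by naming one primary analysis of all randomised participants with available data: either the ANCOVA on multiply imputed scores or an equivalent likelihood model that includes the same auxiliary variables. Apply it to both BDI-II and PHQ-9.
- Impute by arm, with the post-treatment telephone MINI and blind CGI as auxiliary variables. Renaming the ANCOVA a pre-post mixed model is not enough. BAI, QOLI and AAQ-II are web self-reports and will probably be missing in the same people.
- Add a delta-adjusted sensitivity analysis for the unobserved scores, because the auxiliaries reduce the bias but do not remove it.
- Compute the between-group d from the primary estimate, not from observed-case means.
- Reconcile the data-removal sentence under Safety monitoring and reporting with the intention-to-treat claim, and state who can then be analysed.
- Optionally, read the PHQ-9 items by telephone to those who missed the web form. The Trial status section says recruitment has ended, so this reaches only interviews still to come. It changes the mode of administration for those participants and does not recover BDI-II.

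The cost is analysis wording and some extra analysis. Apart from the optional item, no new data collection is needed.
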